#### Data analyses

First, for both the effect analyses on the different outcome variables and moderator and mediator analyses, we will perform multiple regression analyses with baseline levels of the outcome variable as a covariate and condition as a predictor variable. Second, to correct for the clustering of participants within regions and within Halt professionals, the regression analyses will be performed in a multilevel model with the participant as level 1, the professional as level 2, and the region as level 3 cluster variables. Third, to correct for multiple testing, we will implement a Benjamini Hochberg False Detection Rate (FDR; (Benjamini & Hochberg, 1995) correction on the p-values for the respective outcome tests. Fourth, to test for the similarity between conditions, we will compare the two groups of Halt professionals and both conditions on several characteristics (e.g., demographic factors, professionals’ educational level, or youths’ psychological problems). If differences are detected between conditions, we will use propensity score matching (PSM) techniques (Caliendo & Kopeinig, 2008) to match participants in the CAU plus YIM condition to participants in the CAU condition. Lastly, we will implement the Intention-to-Treat (ITT) principle for handling missing data on post-test and follow-up measurements (Detry & Lewis, 2014; Yeatts & Martin, 2015). Thus, we will analyse all missing data of participants according to their assigned condition, regardless of whether the intervention was received or completed (Detry & Lewis, 2014; Yeatts & Martin, 2015). Missing data points will be estimated by performing Full Information Maximum Likelihood (FIML) methods. We will consider the percentage of missing data and patterns of missing data (e.g., missing completely at random) (Bennett, 2001; Schulz & Grimes, 2002).

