**Power Analysis.** To assess the sample size per condition for the primary and secondary outcomes, we performed an a priori power analysis in G*Power 3.1 (Faul et al., 2009). To attain a power level of 0.80 with a significance level of α = 0.05, a total sample size of *N* = 100 is necessary to detect a small effect size (*f* = 0.10) in a linear multiple regression analysis. Meta-analyses that explored the effects of formal mentoring programs on delinquent behaviour and reoffending revealed small overall effects, both *d* = 0.21 (~ f = 0.10) (Jolliffe & Farrington, 2007; Tolan et al., 2014). For moderator and mediator analysis, a larger sample size is required. We performed a priori power analysis a Monte Carlo Power Analysis (Schoemann et al., 2017, p. 384). For a simple trivariate correlation, a total sample size of *N* = 150 is necessary to attain a power level of 0.80 with a significance level of α = 0.05. This would indicate *N* = 75 per condition. However, we aim to include *N* = 150 per condition because (1) we will also include time as a factor in the moderator and mediation models, and (2) we expect relatively high drop-out rates of over 20% (e.g., drop-out at post-test or follow-up measurements) (Furlan et al., 2009).

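### The power analysis treats youths as independent although 62 professionals carry the condition and the planned model is multilevel; restated power should include a design effect

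*Protocol article*

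**What the plan says.** All places are in the protocol article, Study 1.

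- **Power Analysis (under Data analyses).** The authors write "we performed an a priori power analysis in G*Power 3.1". The target is set out as "To attain a power level of 0.80 with a significance level of α = 0.05", and the result is that "a total sample size of *N* = 100 is necessary to detect a small effect size (*f* = 0.10") "in a linear multiple regression analysis". The effect size comes from meta-analyses of formal mentoring that "revealed small overall effects, both *d* = 0.21 (~ f = 0.10"). For moderation and mediation, a Monte Carlo calculation for a simple trivariate correlation gives a total of 150. The aim is then doubled to 150 per condition for two stated reasons: time enters the moderator and mediation models, and "we expect relatively high drop-out rates of over 20" per cent.
- **Data analyses.** The regressions will be run "in a multilevel model with the participant as level 1, the professional as level 2, and the region as level 3 cluster variables". The stated purpose is "to correct for the clustering of participants within regions and within Halt professionals".
- **Design.** Youths are allocated to one of 31 non-YIM-trained or 31 YIM-trained professionals, and the professional's training defines the condition.

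**The concern.** All youths of one professional are in the same condition, so the contrast between conditions is a contrast between two groups of professionals. If outcomes of youths with the same professional are correlated, the variance of that contrast is larger than for independent youths. The planned model allows for this; the power calculation does not. The power statement therefore belongs to a different model from the one to be fitted.

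This is not a detail that an article would leave to a fuller document. The article gives the calculation and lists its reasons for going to 300, and clustering is not one of them. What is at stake is how the result is read: a null finding could be taken as evidence against YIM from a trial believed to have at least 80% power for a small effect.

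**Working it through.** **1. The plan's own figure.** Inputs: two-sided α = 0.05 (sidedness is assumed), power 0.80, f = 0.10. For linear multiple regression the noncentrality is f² × N.

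- With f = 0.10, f² = 0.01. The required total is 787 for one tested predictor and 967 for two. Power at N = 100 is 17% and 13%.
- The two-group formula at d = 0.21 gives 356 per arm, 712 in total.
- N = 100 is reproduced (power 0.803) if 0.10 is entered as f² with two tested predictors. That corresponds to f = √0.10 = 0.32, or d = 2 × 0.316 = 0.63.

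This is a separate error, but it decides what the clustering loss is measured against.

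**2. Cluster size.** 300 / 62 = 4.84 youths per professional as recruited. After 20% drop-out, 300 × 0.8 = 240 and m = 240 / 62 = 3.87.

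**3. Is 300 undermined relative to N = 100?** With equal clusters, DE = 1 + (m − 1) × ICC. At m = 4.84 and an ICC as high as 0.20, DE = 1 + 3.84 × 0.20 = 1.77. Then 100 × 1.77 = 177, and 177 / 0.8 = 222, still below 300.

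**4. Design effect at 240 analysed.** DE = 1 + [(1 + CV²)m − 1] × ICC, and effective N = 240 / DE. The documents give neither the ICC nor the coefficient of variation (CV) of caseload. ICC 0.02 to 0.10 and CV 0 or 0.8 are assumptions. Example: ICC 0.05, CV 0.8 gives 1 + (1.64 × 3.87 − 1) × 0.05 = 1.27, and 240 / 1.267 = 189.

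**5. Power and minimum detectable d.** Power for d = 0.21 uses a noncentral t on 62 − 2 = 60 df with noncentrality 0.21 × √(effective N) / 2. Minimum detectable d at 80% power is about 2 × 2.85 / √(effective N), where 2.85 is the multiplier on 60 df. With an assumed baseline correlation of 0.6, d is multiplied by √(1 − 0.36) = 0.8.

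| Caseload | ICC | DE | Effective N | Power, d = 0.21 | Minimum d | Minimum d, baseline r = 0.6 |
|---|---|---|---|---|---|---|
| Independent | 0 | 1.00 | 240 | 37% | 0.36 | 0.29 |
| Equal | 0.02 | 1.06 | 227 | 34% | 0.38 | 0.30 |
| Equal | 0.05 | 1.14 | 210 | 32% | 0.39 | 0.31 |
| Equal | 0.10 | 1.29 | 186 | 29% | 0.42 | 0.33 |
| CV 0.8 | 0.02 | 1.11 | 217 | 33% | 0.39 | 0.31 |
| CV 0.8 | 0.05 | 1.27 | 189 | 30% | 0.41 | 0.33 |
| CV 0.8 | 0.10 | 1.53 | 156 | 25% | 0.46 | 0.36 |

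The independent row uses 238 df. The last DE is 1.54 if m is rounded to 3.9. With baseline correlation 0.6, power for d = 0.21 is 53% if independent and runs from 49% (equal caseloads, ICC 0.02) to 37% (CV 0.8, ICC 0.10).

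**The case against.** - **The 80% is not claimed at 240 or 300.** It is stated at N = 100 and N = 150. This stands. A reader might infer that clustering makes 300 too small. The documents do not support that: against the stated N = 100 the target absorbs the design effect, as step 3 shows. The defence is only as good as its base, though, and N = 100 does not follow from f = 0.10.
- **Most of the shortfall from 80% is not due to clustering.** This also stands. At d = 0.21 and 240 analysed, power is 37% before any clustering. With equal caseloads, clustering takes off a further 3 to 8 percentage points, so reading the whole gap from 80% to 25% as a clustering effect would be wrong.
- **The lowest figure stacks two assumptions.** The 25% needs both ICC 0.10 and CV 0.8, and the documents give neither. Uneven recruitment is plausible, since sign-up is voluntary and workload affects who gets which case, but that does not establish 0.8. Equal and uneven caseloads therefore have to be shown separately.
- **Inference is protected.** The planned model includes the professional level, so a reader should not conclude that the analysis ignores clustering. The point concerns the power statement only.

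**Conclusion.** The point holds as an omission in the power statement. The calculation is for independent participants, the analysis is not, and no ICC or design effect connects the two. The size is modest: at about 3.9 analysed youths per professional, the design effect is 1.06 to 1.29 with equal caseloads and 1.11 to 1.53 with CV 0.8, over assumed ICCs of 0.02 to 0.10.

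It matters mainly in combination. Once the effect-size error is corrected, the sample is already short for d = 0.21, and clustering has no slack to use up. The absence of an ICC is certain from the text. The magnitudes rest on the assumed ICC, CV and baseline correlation, and on drop-out of exactly 20%, where the article expects more. The total of 150 for mediation cannot be checked, because its input correlations are not given.

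**What to change.** Correct the base calculation first, since a design effect applied to N = 100 would inflate a wrong figure. Then, in Power Analysis:

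- State power at the target sample for the model that will be fitted, with DE = 1 + [(1 + CV²)m − 1] × ICC, m = 3.9 after drop-out, and t on about 60 df.
- Show ICC 0.02, 0.05 and 0.10, with equal and uneven caseloads in separate rows, and label ICC, CV and baseline correlation as assumptions.
- Give the minimum detectable d: 0.38, 0.39 and 0.42 with equal caseloads, and 0.39, 0.41 and 0.46 with CV 0.8. With an assumed baseline correlation of 0.6 these become 0.30, 0.31 and 0.33, and 0.31, 0.33 and 0.36.
- Commit to reporting the observed ICC with the results.

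The cost is wording and a less favourable power figure. Enrolment and the analysis model do not change.

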Strengthening natural mentor-mentee relationships alongside professional involvement has three main benefits over matched mentor-mentee relationships: it is more accessible, durable and empowers the social network. First, it is estimated that about 63–86% of youth can identify a natural mentor (e.g., Dang, 2012; Erickson et al., 2009; Hurd & Zimmerman, 2010; Tucker et al., 2019; Van Dam et al., 2017). This relatively large accessibility could counteract delays typically experienced in formal mentoring due to a larger need and interest in these programs than available volunteer mentors (Raposa et al., 2017; Spencer et al., 2019; Tucker et al., 2019). Second, evidence suggests that youth-initiated relationships are more durable than matched relationships, which increases the likelihood of positive youth outcomes (e.g., Schwartz et al., 2013; Grossman & Rhodes, 2002; Spencer et al., 2016). Approximately 74% of all informal mentors are still involved in the youths’ lives after two years (Van Dam et al., 2017), which could be explained by youths choosing their mentor, contributing to a better mentor-mentee match (Tucker et al., 2019). In contrast, matched mentors and mentees often struggle to form meaningful connections, causing the relationship to end prematurely (e.g., (Grossman et al., 2012; Grossman & Rhodes, 2002). Moreover, youth –particularly those in the juvenile justice system– may be more open to involving a mentor they know and trust (Spencer et al., 2019). Third, strengthening the social network empowers families. Parents who feel supported by their social network experience lower levels of parenting stress and engage in more positive parenting practices, such as monitoring and effective parenting (e.g., Ayala-Nunes et al., 2017; Ghazarian & Roche, 2010; McConnell et al., 2011; Taylor et al., 2015). Consequently, this and the youths’ perception of feeling supported might impact the youths’ behaviour, such as displaying less externalising and delinquent behaviour (e.g., Ghazarian & Roche, 2010; Hagen et al., 2005; Hatch et al., 2020; Wight et al., 2006). Thus, YIM has clear benefits over formal mentoring and has the potential to buffer against the development of juvenile delinquency.

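### The stated N = 100 does not give 80% power for f = 0.10 (d = 0.21); the regression calculation needs roughly 700 to 970, and what the planned 300 delivers is not stated

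*Protocol article*

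**What the plan says.** In the protocol article, Study 1, Data analyses, the Power Analysis paragraph covers the primary and secondary outcomes and reports: "we performed an a priori power analysis in G*Power 3.1". For 80% power at alpha 0.05, its result is that "a total sample size of *N* = 100 is necessary to detect a small effect size (*f* = 0.10") in a linear multiple regression. The next sentence ties that value to meta-analyses of formal mentoring programmes, which "revealed small overall effects, both *d* = 0.21 (~ f = 0.10").

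The same section specifies the model: a regression with the baseline level of the outcome as covariate and condition as predictor, fitted as a multilevel model "with the participant as level 1, the professional as level 2, and the region as level 3 cluster variables".

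The target of 150 per condition is not derived from N = 100. It rests on a separate Monte Carlo calculation for mediation and moderation (N = 150 in total), on time as an added factor, and on expected drop-out of over 20%.

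**The concern.** For two equal groups f = d/2, so d = 0.21 means f = 0.105 and f² = 0.011. The noncentrality in a regression power calculation is f² times N. An effect this small cannot be detected with 80% power in 100 participants, so the stated effect and the stated N cannot both stand.

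The figure is also the only main-effect sample-size calculation in the article. A reader who sees that 100 are needed and 300 are planned could take the main comparison to have a wide margin. If power for the cited effect is well below 80%, a non-significant result says much less about whether YIM works than that reader would suppose.

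**Working it through.** **Inputs from the protocol article.** Power 0.80; alpha 0.05 (sidedness not stated, two-sided taken, one-sided also tried); f = 0.10; d = 0.21; two predictors (baseline and condition); 150 per condition; over 20% drop-out, so at most 240 analysed; 31 + 31 professionals (Design).

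**Assumed, because the article gives no value.** Baseline-outcome correlation r from 0 to 0.7; intraclass correlation (ICC) by professional from 0 to 0.05.

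**Step 1: reproduce N = 100.** Noncentral F with λ = f²·N, and u and N − p − 1 degrees of freedom, where u is the number of tested predictors and p the number in the model.

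| Effect used | u = 1, p = 2 | u = 2, p = 2 | u = 3, p = 3 |
|---|---|---|---|
| f² = 0.10 | 81 | **100** | 114 |
| f² = 0.01 (f = 0.10) | 787 | 967 | 1095 |
| f² = 0.105² = 0.011 (d = 0.21) | 714 | 877 | 993 |

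At f = 0.10 no regression variant gives 100. The smallest is 620, for a one-sided coefficient test. N = 100 appears exactly at f² = 0.10 with both predictors tested together. That effect is f = √0.10 = 0.316, or d = 2 × 0.316 = 0.63, and 0.63 / 0.21 = 3.

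**Step 2: cross-check for d = 0.21 by two means.** n per group = 2 × (1.960 + 0.842)² / 0.21² ≈ 356, so 712 in total. This agrees with 714.

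**Step 3: power at the stated f = 0.10, condition coefficient.** λ = 0.01·N.

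- N = 100: λ = 1.0, power 0.17 (overall two-predictor test 0.13)
- N = 240: λ = 2.4, power 0.34
- N = 300: λ = 3.0, power 0.41

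**Step 4: power at d = 0.21 with baseline adjustment and clustering.** Power = Φ(0.21·√(N/4) / √((1 − r²)·DE) − 1.96), with DE = 1 + (m − 1)·ICC. Cluster size m is 300/62 = 4.84 or 240/62 = 3.87, so at ICC 0.05 DE = 1.192 or 1.144.

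| r | 300, ICC 0 | 300, ICC 0.05 | 240, ICC 0 | 240, ICC 0.05 |
|---|---|---|---|---|
| 0 | 0.44 | 0.38 | 0.37 | 0.33 |
| 0.5 | 0.56 | 0.49 | 0.47 | 0.42 |
| 0.7 | 0.72 | 0.65 | 0.62 | 0.57 |

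**Step 5: correlation needed for 80% power.** Without adjustment or clustering, the minimum detectable d is 2.802 × √(4/300) = 0.323 at 300 and 2.802 × √(4/240) = 0.362 at 240. Setting 0.21 = that value × √(1 − r²) gives r = 0.76 at 300 and r = 0.81 at 240.

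**Step 6: minimum detectable d at 240 over the assumed range.** The lowest is 0.362 × √(1 − 0.49) = 0.26 (r = 0.7, ICC 0). The highest is 0.362 × √1.144 = 0.39 (r = 0, ICC 0.05).

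**The case against.** The strongest reply is that the model adjusts for baseline, so an unadjusted d = 0.21 becomes a larger standardised effect in the regression. That is correct, and it means 300 cannot be said flatly to lack 80% power. A reader might infer that it does; the article does not settle it, because it gives no baseline correlation. But the required correlation is about 0.76 with no loss and no clustering, or about 0.81 at 240, and the article itself expects over 20% loss and plans a multilevel model. Adjustment does not rescue N = 100 either: at 100, even r = 0.85 gives power of only about 0.51.

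A second reply is that a superscript was dropped in print. The link to d = 0.21 rules that out as a full explanation, because f² = 0.10 would not match the cited effect. How the figure arose is still an inference. The match to 100 needs the overall test of both predictors (the condition coefficient alone gives 81), and no software output is shown. A repeated-measures calculation at f = 0.10 can come near 100 (98 with three measurements and an assumed correlation of 0.7), but that is not the analysis named.

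Third, the article nowhere claims a wide margin of power, and it does not say that a null result would be read as no effect. Both are readings that a reader might make, not statements in the text.

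It is also tempting to shrink the effect for incomplete uptake, since "it is estimated that about 63–86% of youth can identify a natural mentor". The documents do not support this. The figure is background from other studies, not an uptake rate for this trial. The Discussion expects every case to reach at least the second implementation level. The cited d = 0.21 may already include non-uptake, so a discount could count it twice.

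Clustering is a secondary matter. With four to five youths per professional and an assumed ICC of 0.05, it lowers power by about 0.04 to 0.08.

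**Conclusion.** The stated main-effect sample size is wrong on the article's own inputs, by a factor of about seven to ten: 714 to 967 against 100. This needs no assumption beyond the printed alpha, power, effect and model (two-sided); even a one-sided coefficient test at f = 0.10 needs 620. The figure is consistent with f² = 0.10 having been used where f = 0.10 was meant, but the cause is not shown.

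The conclusion about 300 is conditional. At f = 0.10 taken as the effect in the regression, power for condition is about 0.41, or 0.34 with 20% loss. At d = 0.21, with r from 0 to 0.7 and ICC from 0 to 0.05 (both assumed), it is about 0.38 to 0.72 at 300 and 0.33 to 0.62 at 240. Power of 80% would require a baseline correlation above that range. The planned false-discovery-rate correction is not counted in these figures and can only lower them. The target of 300 itself is not shown to be mistaken, since it was set on other grounds.

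**What to change.** - Withdraw the statement that a total of 100 is enough for f = 0.10.
- Keep the target of 300 and restate what it provides for d = 0.21, with the assumed baseline correlation, ICC, cluster size and loss named. Over r = 0 to 0.7 and ICC = 0 to 0.05, power is about 0.38–0.72 at 300 and 0.33–0.62 at 240, and the minimum detectable d at 240 is about 0.26–0.39.
- Base the restated calculation on the test of the condition coefficient, not on the overall test of both predictors.
- State that a non-significant main effect will be reported through its confidence interval and not as evidence of no effect.

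The cost is a text correction. No participants, visits or measurements are added, but the stated power becomes less favourable.

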
#### Data collection and procedure

Both recruitment and data collection started on September 1st, 2022. Recruitment will stop after 15 months because researchers strive to complete pre- and post-tests within 18 months. Follow-up measurements can occur up to 24 months after the start of the data collection. Participants will be asked to fill out three questionnaires: before the initial meeting (baseline), 100 days after baseline (post-test), and nine months after baseline (follow-up). After giving consent via the flyer, participants will automatically be referred to the first online questionnaire and instructed to complete it before their initial meeting at Halt. After that, researchers will approach eligible participants for post-test and follow-up measurements (see Fig. 2). All questionnaires will be administered in Dutch and will take approximately 30 min to complete. Participants will receive €7,50 per completed questionnaire; when they complete all questionnaires, they may win AirPods (€130).

Complementary to the questionnaires, we will receive pseudonymised youth case data from Halt’s registration system. Professionals in both conditions will register the characteristics of the Halt intervention (e.g., number of meetings, type of crime) and the risk assessment (i.e., Halt-SI) per youth case. In the CAU plus YIM condition, professionals will additionally register characteristics of YIM (e.g., the reaction of youth to YIM, caregivers’ approval of YIM, and the youth’s relation to the YIM (e.g., uncle, grandmother)). Most importantly, professionals will report the steps they have taken to implement YIM: (1) the YIM question was asked (“Who, an adult aside from your caregiver(s), can you turn to if necessary?”), (2) steps were taken to support youth in identifying and nominating a YIM, such as the network or YIM assignment, and (3) a YIM was positioned in an official meeting with all parties. Note that the third level of implementation is only possible if youths can identify and nominate a mentor.

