It is also crucial to mention three potential challenges. First, allocating youths to either condition (i.e., to a non-YIM-trained or YIM-trained professional) is non-random. Random allocation is impossible because Halt’s distribution office considers professionals’ workload. This might lead to an unequal division of youth cases over conditions and, thus, less comparable conditions. Differences between conditions could then possibly be explained by confounding factors instead of the effects of YIM, such as differences in the severity of the youth case (Flannelly et al., 2018). To ensure comparable conditions, we will match professionals in the CAU plus YIM condition within each region to professionals in the CAU condition. Nevertheless, we must be cautious of drawing causal inferences. We will also address other confounding factors between conditions, such as differences in the number of sessions or types of activities. Second, baseline and post-test measurements will occur without the knowledge of the implementation level of YIM in the CAU plus YIM condition. We will assess three levels of implementation steps taken by a professional: (1) the YIM question was asked, (2) steps were taken to support youth in identifying and nominating a YIM, and (3) a YIM was positioned in an official meeting. External factors can influence these steps, such as a youth not being able to identify or nominate a YIM. If this is the case, it is impossible to position a YIM. We will, however, instruct professionals to explain and motivate YIM in all youth cases, possibly leading to the positioning of a YIM. Overall, we expect that all cases will at least have the second level of implementation. However, due to the natural course of YIM, we cannot rule out natural variation in the level of implementation. Because this might impact the findings, we will consider these implementation levels in our analyses. Moreover, these implementation levels will allow us to explore whether different elements of YIM affect the approach’s effectiveness. Third, all participants will voluntarily sign up for the study, potentially leading to a selective pool of more intrinsically motivated participants. Even though Halt has a broad population, with varying degrees of problems and different types and severity of offences and crimes, the registered group might not entirely represent the Halt population. Potentially, youth with more severe problems might be missed. This would, however, apply to both conditions – if this were to be the case. Hence, to appeal to the entire population at Halt, we will offer a monetary contribution per completed questionnaire and the chance to win the grand prize, namely AirPods. Fourth, a challenge in the focus group interviews is that being in a group, people might not feel comfortable enough to share their true perspectives and opinions on working with the innovation. Moreover, some individuals could be more dominant in the conversation than others, which might discourage some individuals from actively participating. To encourage active participation and a comfortable environment, we will perform *think-pair-share* techniques (Kagan, 1994; Lyman, 1981) in a neutral environment without the involvement of YIM and Halt management.

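### The 0.80 power claim, justified by d = 0.21, makes no allowance for YIM-arm youths without a positioned mentor, and is not met for d = 0.21 even with full uptake

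*Protocol article*

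**What the plan says.** **Power.** The Power Analysis paragraph of the protocol article (Study 1, Data analyses) opens its claim with "To attain a power level of 0.80 with a significance level of α = 0.05" and gives a total of 100 for f = 0.10 in a linear multiple regression, for the primary and secondary outcomes alike. The effect size is justified by "Meta-analyses that explored the effects of formal mentoring programs on delinquent behaviour and reoffending revealed small overall effects, both *d* = 0.21", equated there with f of about 0.10. A separate mediation calculation gives 150 in total. The plan then states "we aim to include *N* = 150 per condition", because time enters the moderator and mediation models and drop-out of over 20% is expected. Incomplete mentor uptake is not mentioned.

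**Analysis set.** The Data analyses section invokes intention-to-treat (ITT) and analyses participants "according to their assigned condition, regardless of whether the intervention was received or completed".

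**Delivery of YIM.**
- Under Conditions, YIM is an activity that can be selected, and a youth may react negatively to it.
- Data collection and procedure defines three implementation levels: the question asked, support in identifying and nominating a mentor, and a mentor officially positioned. It adds: "Note that the third level of implementation is only possible if youths can identify and nominate a mentor".
- The Discussion says "Overall, we expect that all cases will at least have the second level of implementation". It makes no such statement for the third level and accepts that this variation may affect the findings.
- The only figure bearing on uptake is in the background section on youth-initiated mentoring: "it is estimated that about 63–86% of youth can identify a natural mentor".

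**The concern.** An analysis by assignment estimates the effect of being allocated to a YIM-trained professional, averaged over youths with and without a positioned mentor. If the planning effect is what a mentor does for a mentored youth, the effect to be detected is smaller in proportion to the share positioned. The required sample size rises with the inverse square of that share.

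The protocol anticipates incomplete positioning but leaves it out of a power calculation that it prints in full. At stake is how a null result is read. With the stated 0.80, a non-significant comparison looks like reasonable evidence that YIM does not work. With much lower power, it could simply have missed an effect of the size used to plan the trial.

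**Working it through.** **Inputs from the protocol article:** α = 0.05, power 0.80, N = 100, f = 0.10, d = 0.21, 150 per condition and drop-out over 20% (Power Analysis); 63–86% able to identify a natural mentor (Youth-initiated mentoring).

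**Assumptions added here:** two-sided test, equal arms, independent youths (no clustering), no multiplicity correction, drop-out of exactly 20% (300 × 0.80 = 240).

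**1. The plan's own figure.** For a regression test, the noncentrality is λ = f² × N. For a two-group contrast with equal arms, f² = d²/4.
- f = 0.10 gives f² = 0.01. With one tested predictor, 80% power needs N = 787.
- d = 0.21 gives f² = 0.21²/4 = 0.011, which needs N = 714.
- N = 100 comes out exactly if 0.10 is entered as f² with an overall test of two predictors. As a pure two-group contrast, f² = 0.10 would mean d = 2 × √0.10 = 0.63.

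So N = 100 does not correspond to d = 0.21.

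**2. Power for d = 0.21 with full uptake.** Power is approximately Φ(d√N/2 − 1.96). At N = 300: 0.21 × 17.32/2 = 1.819, and Φ(−0.141) = 44%. The exact noncentral calculation gives 18.0% at N = 100, 36.7% at N = 240 and 44.2% at N = 300.

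**3. Illustration with incomplete uptake.** Suppose d = 0.21 applies per mentored youth, levels 1 and 2 have no effect, and a share c of the arm has a mentor positioned. The effect by assignment is then c × 0.21:
- c = 0.86: 0.86 × 0.21 = 0.181
- c = 0.63: 0.63 × 0.21 = 0.132

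| Share positioned | d by assignment | Power, N = 300 | Power, N = 240 | Power, N = 300, baseline correlation 0.5 (assumed) | Total N for 80%, unadjusted |
|---|---|---|---|---|---|
| 1.00 | 0.210 | 44.2% | 36.7% | 55.3% | 714 |
| 0.86 | 0.181 | 34.4% | 28.6% | 43.7% | 966 |
| 0.63 | 0.132 | 20.8% | 17.5% | 26.1% | 1,796 |

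The required N grows by 1/0.86² = 1.35 and 1/0.63² = 2.52. The last column shows scale only and is not a proposal.

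**4. Smallest detectable effect at N = 300, 80% power.** Unadjusted: (1.96 + 0.84) × √(2/150) = 0.32. With an assumed baseline correlation of 0.5: 0.32 × √(1 − 0.25) = 0.28. Both are before clustering and drop-out.

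**The case against.** **The dilution may already be in d = 0.21.** The article calls it an overall effect of formal mentoring programmes. The same article describes such programmes as short of volunteers and prone to early endings, so imperfect delivery may be built in. A reader might infer that d = 0.21 is the full effect in mentored youths. The article does not say so, and the cited meta-analyses are not at hand. This stands: the size of the loss is unknown.

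**The 63–86% range is not a forecast for this trial.** A reader might infer that 14–37% of the YIM arm will never have a mentor. The range is background literature on naming a natural mentor. Halt professionals actively help youths identify one, which could raise the share; refusal or non-selection of YIM could lower it. The article gives no expected share, so the range can serve only as an illustration.

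**Levels 1 and 2 may work.** All cases are expected to reach level 2, and the primary outcomes are perceived social support and support seeking, which supported network mapping might affect. Zero effect below level 3 is therefore an assumption, and the loss shown is the most that dilution would cause at each share.

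**The N = 100 route cannot carry the dilution.** It is tempting to shrink the f² of 0.10 by the square of the uptake. That reading fails: N = 100 reproduces with a two-predictor test, and one planned predictor is the baseline outcome, whose association uptake does not weaken. Shrinking only the condition part (0.011) takes power at N = 100 from 80% to 79% or 77%.

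**The larger problem is elsewhere.** N = 100 does not fit d = 0.21, and N = 300 was built from the mediation figure. Also, d = 0.21 concerns delinquency, a secondary outcome, and no effect size is given for the primary scales. All true. But correcting the effect-size entry alone would still leave power stated for full uptake, and the paragraph applies its calculation to primary and secondary outcomes together.

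**The protocol acknowledges variable implementation** and will consider the levels in its analyses. That helps exploration but does not change the power of the comparison by assignment.

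**Conclusion.** The point holds in a limited form. The power paragraph makes no allowance for youths without a positioned mentor, while the analysis is by assignment and the protocol itself foresees such youths. Independently of uptake, the claimed 0.80 is not met for the effect cited in its support: about 18% at N = 100, 44% at N = 300 and 37% at N = 240, unadjusted.

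The further loss from incomplete uptake is conditional. It reaches 21–34% power at N = 300, or 17.5–28.6% at N = 240, only if d = 0.21 is a per-mentored-youth effect, the earlier levels do nothing, and uptake lies in the general 63–86% range. If either of the first two assumptions fails, the loss is smaller. Baseline adjustment would raise all these figures; clustering and the false-discovery correction are left out and would tend to lower them. The documents support calling the uptake assumption unstated, but not any particular size of dilution.

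**What to change.** In the Power Analysis paragraph:

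1. Replace the 0.80 claim with the power at the planned N = 300, or with the smallest effect by assignment that N = 300 can detect: d of about 0.32 unadjusted, or 0.28 with an assumed baseline correlation of 0.5, before clustering and drop-out.
2. State the share of the CAU plus YIM arm expected to have a mentor positioned, and its source.
3. State whether d = 0.21 is taken as a programme-level or a per-mentored-youth effect. Scale it by the share positioned only in the second case.
4. Describe the ITT result as the effect of assignment to a YIM-trained professional, and report it with its confidence interval and the share positioned.

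The cost is some rewording and a less favourable stated power. Professionals already register whether a mentor was positioned, so no new data are needed, and no extra enrolment is proposed.
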